### Trial design

This is a simple parallel group multicentre phase 3, double-blind, randomised, placebo-controlled trial which includes a 96-week exposure period. Detailed evaluations of all participants will take place at screening, baseline, 24, 48, 72 and 96 weeks (figure 1). Participants will also attend on a 12 weekly basis to collect supplies of Investigational Medicinal Product (IMP). Participants will be randomly allocated to receive either exenatide extended release 2 mg subcutaneous injection (Bydureon) once weekly for 96 weeks n=100, or exenatide extended release placebo subcutaneous injection once weekly for 96 weeks n=100. In addition, participants will be randomised using a minimisation algorithm (with a random element incorporated) balancing by research site, participants with greater (Hoehn and Yahr stage 2.5) or lesser (Hoehn and Yahr stage 2.0 or less) PD severity (in the ON medication state), and participation in the substudies (remote monitoring, imaging or not participating).

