### Assessment procedures

After the screening visit, the named site clinical staff member will call the participant to remind them of the need to stop taking their regular PD medication prior to their next trial visit and to attend in a fasted state (prior to visits 2, 4, 6, 8, 10). The MDS-UPDRS part 3 and Timed Walk assessments will be initially performed in the OFF state. This assessment in both the ‘OFF’ and ‘ON’ states will be performed with video recording to facilitate the possibility of a re-review if necessary. Remote monitoring assessments will be conducted at this point at selected sites in patients consenting to participate in this substudy. While waiting for medications to work, participants will self-complete the MDS-UPDRS parts 1, 2 and 4, Parkinson’s Disease Questionnaire-39, EQ-5D-5L and Client Service Receipt Inventory. The MDS-UPDRS part 3 and Timed Walk assessments will be repeated 1 hour after the participant has taken their routine medications—the ON medication state. After completion of the MDS-UPDRS and Timed Walk assessments in the ON medication state, each participant will be assessed using the MoCA, NMS scale, Unified Dyskinesia Rating Scale and PHQ-9. This will occur in alternate postrandomisation assessments (at visits 2, 4, 6, 8, 10). At selected centres participants in the CSF substudy will have a CSF sample taken via lumbar puncture. Ten weeks after the last trial medication administration, a staff member will call the participant to collect details of any AEs that have occurred after the participant stops taking the trial medication. Participants will complete the 3-day Hauser Diary prior to visits 2, 6 and 10 and return the diary back to the research team at the respective study visits. At each of the visits 2, 4, 6, 8 and 10, a blood sample will be collected and processed for storage for future analysis.

The DaTSCAN imaging substudy will be performed at the UCLH site on all consenting substudy participants; scans will be performed prior to visit 2 and after visit 10.

The option for performing a remote assessment will be provided to patients for safety monitoring visits in view of the coronavirus pandemic.

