### Sample size

The sample size is based on the detectable effect size (primary outcome is the MDS-UPDRS motor subsection in the OFF medication state) for a two-arm (exenatide vs placebo) parallel-group trial design. The calculations assume a common SD of 13.5, and a correlation of 0.70 between baseline and follow-up MDS-UPDRS measurements. These estimates are reasonable based on data from the previous exenatide-PD trial.^14^ On this basis, 160 evaluable participants divided equally between the two groups is sufficient to detect a difference of 5.0 MDS-UPDRS part 3 points in the OFF medication state between the two groups adjusting for baseline MDS-UPDRS part 3 OFF scores, with 90% power and at a significance level of 0.05. Assuming 20% attrition (withdrawal/lost to follow-up), 200 participants will be recruited. Participants who withdraw from the trial will not be replaced. Participants who withdraw from trial treatment should remain in the trial for the purpose of follow-up and data analysis. This effect size is a reasonable expectation based on the previously collected pilot data and would represent a clear demonstration of the efficacy of exenatide on the motor severity of PD.

It is also anticipated that the difference in scores in the ON medication state will be greater at 96 weeks than at the earlier time points. The expected rate of change in PD severity in the first 5 years after PD diagnosis in the ON medication state is 1 MDS-UPDRS part 3 point per year. A predicted advantage of 2 points in ON scores over 96 weeks would thus equate to an advantage in the rate of disease progression above and beyond that achievable with conventional dopaminergic medication and would be a further clear signal that continued use of exenatide is consistent with not only long-term disease modifying effects, but even demonstration of a small change of 2.5 points in the MDS-UPDRS motor score would constitute a clinically important difference^24^ and potentially an advantage in day to day functional impairment and overall improvement in quality of life in the short term.

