### Statistical analysis

A full statistical analysis plan will be written and approved by the TSC prior to database lock. All analyses will be undertaken according to a modified intention-to-treat principle in accordance with the randomised intervention. The threshold for the analysis population will be participants who complete 12 weeks on treatment and for whom outcomes are available.

Primary outcome analysis will evaluate the impact of treatment allocation (exenatide or placebo) on the difference between MDS UPDRS part 3 OFF medication scores at 96 weeks follow-up adjusting for baseline. The analysis will use a mixed-model approach incorporating information from all follow-up visits that adjusts for baseline Hoehn and Yahr status and the baseline raw value of each outcome measurement. Site will be included as a random effect to account for variability in outcomes between sites, and a random patient/subject effect will accommodate the correlation between repeated outcome measures on the same patient. A significance level of 5% will be used to judge significance for the primary outcome measure.

A planned secondary analysis will compare the difference in MDS-UPDRS part 3 OFF medication scores according to randomisation allocation at 96 weeks, with the scores at 48 weeks. An increase in the advantage at 96 weeks compared with 48 weeks would be evidence that the active drug was slowing down disease deterioration rather than having symptomatic effects only. This could translate to a major population advantage in terms of reduction of morbidity and mortality.

Analyses of the remaining secondary/exploratory outcomes will be undertaken similarly for the difference between groups according to treatment allocation at 48 and 96 weeks follow-up adjusting for baseline values of each outcome, and confounding factors such as LED differences between groups.

Further exploratory analyses will consider whether exenatide can be thought of as disease modifying by comparing slopes between groups at prespecified periods.

A sensitivity (per-protocol) analysis will be performed for the primary outcome measure and will only include those participants who completed the trial in accordance with the approved protocol.

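### The primary model omits substudy participation, one of the three minimisation factors; if that factor is prognostic, the reported standard error is slightly too wide

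*Protocol article*

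**What the plan says.** Under Trial design, the protocol article describes a "minimisation algorithm (with a random element incorporated") with three balancing factors. The first two are given as "balancing by research site, participants with greater (Hoehn and Yahr stage 2.5) or lesser (Hoehn and Yahr stage 2.0 or less) PD severity". The third is "participation in the substudies (remote monitoring, imaging or not participating").

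Under Statistical analysis, the primary analysis is a mixed model over all follow-up visits that "adjusts for baseline Hoehn and Yahr status and the baseline raw value of each outcome measurement". The article adds: "Site will be included as a random effect to account for variability in outcomes between sites". A random patient effect handles the repeated measures. Two of the three minimisation factors therefore appear in the model and the third does not.

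The same section says that a full statistical analysis plan will be approved before database lock. It says that the remaining secondary and exploratory outcomes will be analysed in a similar way, adjusting for baseline and for confounders, of which levodopa equivalent dose is named as one example.

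**The concern.** When allocation is forced to balance on a factor, that factor contributes little or nothing to chance differences between the arms. If the model then leaves the factor out, whatever it explains of the outcome stays in the error variance. The model-based standard error is then larger than the true sampling variability of the treatment estimate. The usual principle is to analyse with the factors used to randomise. The article follows it for site and Hoehn and Yahr stage and departs from it, without comment, for substudy participation.

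At stake is a small loss of efficiency in the primary test. The article spells out the model term by term, including which effects are random, so an analysis plan that follows it would inherit the gap.

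**Working it through.** **Inputs.** From Sample size: "a common SD of 13.5, and a correlation of 0.70 between baseline and follow-up MDS-UPDRS measurements", a target difference of 5.0 points, 90% power, a significance level of 0.05 (taken as two-sided), 160 evaluable participants (80 per arm) and 20% attrition. The share of residual variance explained by substudy participation, R², is not in the article. It is assumed here to lie between 0 and 0.05.

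**The plan's own figure.** The residual SD after baseline adjustment is 13.5 × √(1 − 0.70²) = 9.64. The number per arm is 2 × (1.960 + 1.282)² × 9.64² / 5² = 78.1, rounded up to 79, or 158 in total against the stated 160. Power at 80 per arm is 90.7% by the normal approximation (90.3% by the noncentral t). Recruitment is 160 / (1 − 0.20) = 200. The stated figures reproduce.

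**Effect of omitting a balanced factor.** With perfect balance at 80 per arm:

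- Reported SE with the factor omitted: 9.64 × √(2/80) = 1.524, whatever R² is.
- True SE of the estimate: 1.524 × √(1 − R²).
- Excess of reported over true SE: 1/√(1 − R²) − 1.
- Type I error with the factor omitted: 2 × [1 − Φ(1.960 × 1.524 / true SE)].
- Power omitted: Φ[(5 − 1.960 × 1.524) / true SE]. Power included: Φ[5 / true SE − 1.960].

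| Assumed R² | True SE | Excess of reported SE | Type I error, omitted | Power omitted | Power included |
|---|---|---|---|---|---|
| 0 | 1.524 | 0% | 0.050 | 90.7% | 90.7% |
| 0.01 | 1.517 | 0.5% | 0.049 | 90.8% | 90.9% |
| 0.02 | 1.509 | 1.0% | 0.048 | 90.9% | 91.2% |
| 0.05 | 1.486 | 2.6% | 0.044 | 91.2% | 92.0% |

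**In participants.** At R² = 0.05 the unadjusted analysis of 160 has z = (5 − 1.960 × 1.524) / 1.486 = 1.355. An adjusted analysis reaches the same power with 2 × (1.960 + 1.355)² × 9.64² × 0.95 / 5² = 77.6 per arm, about 155 in total. The saving is about 5. The same calculation at R² = 0.01 gives about 159, a saving of about 1.

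**Simulation check.** Allocation was minimised on six sites, Hoehn and Yahr stage and a three-level substudy factor, with 160 participants and 3,000 runs per scenario. A single 96-week analysis of covariance with fixed site effects stood in for the mixed model. The allocation probability (0.8), the factor frequencies and the independence of substudy from site were assumptions. At R² of 0, 0.02 and 0.05, type I error was 0.057, 0.053 and 0.046 with the factor omitted, and 0.055, 0.055 and 0.049 with it included (Monte Carlo error about 0.004). The power gain from including it was 0.0, 0.3 and 1.0 points. Within that error, direction and size agree with the table.

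**Cost of the term.** In the fixed-site version, treatment, baseline score, Hoehn and Yahr stage and six site terms use 9 degrees of freedom and leave 151 of 160. Two more terms leave 149.

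**The case against.** The strongest objection is that nothing in the article shows participation to be prognostic once the other terms are in the model, and some of what it says suggests a weak residual effect. On imaging it states: "The DaTSCAN imaging substudy will be performed at the UCLH site on all consenting substudy participants". On the digital measures: "Remote monitoring assessments will be conducted at this point at selected sites in patients consenting to participate in this substudy". Site is already modelled, so it may absorb part of any substudy effect. This stands, and it is why the range starts at zero. It does not remove the point: both substudies take only consenting patients, so participation also varies within sites, where a site effect cannot reach it.

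Balancing on participation may also serve to keep the arms comparable within the substudies rather than to control prognosis. That is a fair inference, but the article does not say so. In addition, the random element, attrition and the requirement of 12 weeks on treatment for the analysis population will leave balance imperfect, so the table is an upper bound at each R².

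The unseen analysis plan may already include the term. That would settle the matter. The article's covariate list is nevertheless explicit enough to be compared with its own randomisation scheme.

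A reader might infer several stronger things that the article does not support:

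- That the standard error is certainly wrong. At R² = 0 there is no mismatch.
- That the false-positive rate is inflated or the estimate biased. Any error runs in the conservative direction.
- That the precision gained by balancing is lost. Balance reduces the true variance whether or not the factor is modelled. Power with the factor omitted still rises from 90.7% to 91.2% as R² goes from 0 to 0.05, so R² × 160 = 8 participants overstates the loss at R² = 0.05.
- That every secondary analysis is affected. Their adjustment list is open-ended, so omission there is not firmly stated.

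**Conclusion.** The omission is real: the stated primary model carries two of the three minimisation factors and gives no reason for leaving out the third. Its effect is conditional and small. For an assumed R² of 0 to 5% beyond baseline score, Hoehn and Yahr stage and site, the reported standard error is 0 to 2.6% too wide. Even at R² = 0.10, beyond the assumed range, the excess would be 5.4% and the type I error 0.039, still on the conservative side. Neither the validity of the primary comparison nor the planned sample size is in question. The figures rest on near-perfect balance in the analysed set and on a single-visit approximation to the mixed model. This is a minor point.

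**What to change.** Before database lock, state in the analysis plan that substudy participation enters the primary model as a three-level fixed effect beside Hoehn and Yahr stage, baseline score and the random site effect. The secondary models that follow the primary one should carry the same term. Use the coding held by the randomisation system: as printed, the levels do not say how someone in both remote monitoring and imaging is classed. If the factor is left out on purpose, a sentence giving the reason would be enough. The change costs 2 degrees of freedom and one line of text. It needs no new data, because the variable was required for allocation, and no change to the sample size.

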### Data management

Data will be entered in the Exenatide-PD3 database by delegated staff at participating sites and members of the Exenatide-PD3 TT at CCTU. Participants will be given a unique trial PIN (Exnnn). Data will be entered under the Personal Identification Number onto the central database (InferMed’s MACRO stored on the servers based at UCL). The database will be password protected and only accessible to members of the Exenatide-PD3 TT and external regulators if requested. Video recordings of the MDS-UPDRS will be uploaded onto a secure cloud held by Machine Medicines Technologies (MMT) and used for quality control purposes. Appropriate contractual agreements covering data protection are in place with MMT. All data storage will adhere to GDPR and the Data Protection Act 2018.

An IDMC will be convened including at least three individuals independent from the TT and sponsor who have experience in the conduct of clinical trials for PD. The IDMC will review the trial results and make a recommendation to the TSC regarding continuation/stopping of the trial based on safety data. A statistician independent of the Exenatide-PD3 TT at CCTU will generate summaries of accumulating trial data for the IDMC to review.

UCL is the trial sponsor and has delegated the duties as sponsor to CCTU via a signed letter of delegation. The trial sponsor will take on responsibility for securing the arrangements to initiate, manage and finance the trial. Trial oversight is intended to preserve the integrity of the trial by independently verifying processes and prompting corrective action where necessary. In multicentre trials this oversight is considered and described both overall and for each recruiting centre by exploring the trial dataset or performing site visits. The TT will assist with developing the design, coordination and day-to-day operational issues in the management of the trial, including budget management. The TMG will assist with developing the design, co-ordination and strategic management of the trial. The independent TSC is the independent group responsible for oversight of the trial in order to safeguard the interests of trial participants. The TSC will provide advice to the chief investigator, CCTU, the funder and sponsor on all aspects of the trial through its independent Chair. The IDMC is the only oversight body that has access to unblinded accumulating comparative data. The IDMC will be responsible for safeguarding the interests of trial participants, monitoring the accumulating data and making recommendations to the TSC on whether the trial should continue as planned. The membership, frequency of meetings, activity (including trial conduct and data review) and authority of each committee will be covered in their respective terms of reference.

## Ethics and dissemination

The trial protocol, all informed consent forms and any material to be given to the prospective participant have received REC (initial date of approval 15/10/2019, REC reference no.19/SC/0447), and other regulatory approvals (EudraCT 2018-003028-35). Further, the trial was registered in clinicatrials.gov NCT004232969 and in ISRCTN (reference 14552789). Subsequent amendments to these documents will be submitted for further approval. The same/amended documents will be submitted for additional local permissions at each clinical site.

This is a Clinical Trial of an IMP as defined by the EU Directive 2001/20/EC. Therefore, a clinical trial authorisation is required in the UK and the trial protocol will therefore be submitted to the UK regulatory authority (MHRA). The progress of the trial, safety issues and reports, including expedited reporting will be reported to the MHRA as required. The protocol, PIS and informed consent forms on local headed paper, the REC/HRA and MHRA approvals, schedules of funding and activity (and other trial documentation as needed) have been submitted to the relevant NHS Trust Research & Development department of each participating site or to other local departments for approval.

Participants will be provided with a PIS and given time to read it fully. Following a discussion with a medical qualified investigator or suitable trained and authorised delegate, any questions will be satisfactorily answered and if the participant is willing to participate, written informed consent will be obtained (online supplemental material 2). During the consent process, it will be emphasised that the participant is free to refuse to participate in all or any aspect of the trial, at any time and for any reason, without affecting their treatment. The risk/benefit profile of the trial will be regularly monitored. Consent will be resought if new information becomes available that affects the participant’s consent in any way.

10.1136/bmjopen-2020-047993.supp2Supplementary data

The rights of the participant to refuse to participate in the trial without giving a reason will be respected and after the participant has entered the trial, the clinician remains free to give alternative treatment to that specified in the protocol, at any stage. The participant remains free to change their mind at any time about the protocol treatment and follow-up without giving a reason and without prejudicing their further treatment. All participants will be made aware of the known adverse reactions.

## Discussion

A parallel group design with a washout period has been used previously in the evaluation of potential neuroprotective agents.^25 26^ and this was chosen as the design for the previous phase 2 trial. This design is subject to possible long duration symptomatic effects and a lengthy washout period potentially impacts on patient retention and cannot necessarily distinguish a true neuroprotective effect from a symptomatic effect (in view of preservation of healthy behaviours with long term impacts such as exercise).^27^ An alternative approach which we have adopted here is a ‘long-term simple’ design, with longer-term follow-up to look for a cumulative advantage emerging with prolonged treatment exposure, given the natural history of PD being that of progressive accumulation of motor and non-motor disability.^28^ This design helps build on the previous successful clinical trials of exenatide which have introduced a novel, cost effective way of evaluating the potential for disease modifying drugs in PD by recruiting patients already in receipt of conventional dopaminergic treatment, rather than restricting recruitment to incident cases yet to receive dopaminergic treatment. Using this approach, we have successfully demonstrated the potential for rapid recruitment, and improved retention of participants enabling more complete follow-up, and a statistically significant advantage in motor scores in people randomised to exenatide over a 48-week period of treatment exposure. We have considered that an exposure period of 96 weeks would allow exploration of long-term effects of exenatide exposure, while being the maximum period that participants would be willing to accept being allocated placebo. Furthermore, this will provide the opportunity to evaluate whether the 48-week data previously published can be replicated and whether effects at 96 weeks are similar to or greater than those seen at 48 weeks and other earlier time points.

Many trials have attempted to evaluate the potential for disease modification using drugs with broad mechanisms of action. The majority have either failed to demonstrate clinical efficacy or provided inconclusive results. Some pertinent reasons for this are a failure of the investigated agent to reach and engage its target and lack of objective measures of true clinical disease progression. Clinical endpoints such as the MDS-UPDRS scale are necessary to ultimately confirm relevance; however, these scales lack sensitivity for capturing disease modification unless very long term follow-up data are collected. While our approach of following patients for 2 years in this trial will partially mitigate some of this, the addition and to an extent validation of more detailed approaches through a number of sub studies (imaging, CSF analysis for target engagement and drug levels, and device assisted measurements of real-life motor function) could ultimately provide more holistic and definitive metrics for determining if exenatide does in fact deliver disease modification in PD. This more comprehensive approach to approaching assessments and the consistent signal of benefit noted in two earlier trials provide grounds for optimism that the primary outcome will be achievable. The study opened to recruitment in January 2020 and we expect completion of study analysis by Q3 2024.
